### Informed consent

Written informed consent for study participation will be obtained at 1 to 7 days after admission at our department.

Participants will be informed that successful completion of the baseline tests is required prior to randomisation to an intervention group.

### Eligibility criteria

Participants will have ICUAW due to defined CIP and/or CIM (for details see Table 1). The diagnosis of CIP and/or CIM will be confirmed by a neurologist according to published criteria [9, 24] at ICU prior to admission or after admission to our post-acute ICU.

### Outcome measures

Primary efficacy endpoints are walking ability and activities of daily living.

We define our endpoint walking ability with a category of ≥3 on the Functional Ambulation Categories (FAC; 0–5 score range) [25–27]. We use this scale to measure walking ability because in a recent cohort study it has been shown to be a very feasible tool to describe the ability to walk in different settings, such as ICU, post-acute rehabilitation and also at follow-up [26].

We will use the Functional Status Score for the Intensive Care Unit Scored (FSS-ICU; 0–35 score range) [28] to measure elementary activities of daily living. We will use this scale because in a recent cohort study the FSS-ICU was also very feasible, reliable and also predictive (for important aspects of daily living) in different settings and stages such as ICU, post-acute rehabilitation and post-acute care [26].

Our secondary endpoints comprise scales with a comprehensive spectrum of impairments, activities and participation for this population (see Table 2). We will measure the ability to stand up by documenting the ability to stand up from a standardised chair independently (STS) [27]. We will measure muscle strength of the upper (shoulder, elbow and wrist) and lower limb (hip, knee and ankle) using the Medical Research Council (MRC) sum score and calculate and provide a MRC sum score for the upper and also for the lower limbs [1, 27, 29]. We will measure the handgrip strength for both hands using a hand dynamometer (Jamar handgrip dynamometer; Sammons Preston Rolyan, Bolingbrook, IL, USA) [27, 30–32]. We will use the Physical Function for the Intensive Care Unit Test-Scored (PFIT-S) [33] to measure specific ICU impairments. We will assess quality of life using the EQ-5D [34] and measure participation with the Reintegration to Normal Living Index (RNL-Index) [27, 35, 36]. All of these measures are frequently used in research and/or clinical practice dealing with this patient group. Table 2 gives a detailed overview of the variables used at each time point of study and the data collection schedule.

### Assessment of safety and adverse events

At each assessment the following parameters will be systematically recorded: recurrent, fatal or nonfatal cardiovascular or cerebrovascular events; referral to an acute hospital; and death. After each intervention, the treating physiotherapist will record the presence of self-reported pain, fatigue, dizziness and number and nature of falls, and note any other adverse events. Additionally, oxygen saturation, mean arterial pressure, and heart rate will be documented for every therapy session.

### Standardisation of assessments

Blinded assessors have systematically undergone competency training to ensure standardisation of data collection methods. This included theoretical learning about the assessments, demonstration and practice on volunteers (patients with ICUAW in our post-acute ICU) under the supervision of the study’s clinical research coordinators. Successful completion of competency training was confirmed by a competency checklist.

### Data collection

Masked outcome data are collected by blinded assessors at baseline (T0), after 2 weeks of therapy (T1), after a 3-week follow-up (FU1), at 6-month follow-up (FU2) and at 12-month follow-up (FU3) (see Fig. 2 and Table 2). Outcome data will be double-entered into two data tables by masked researchers who have no knowledge of, or access to, identifiable participant information or treatment assignment. The two data entries are compared, corrections made and also tested for inter-rater reliability between the blinded assessors.

### Randomisation and concealment of allocation

Each study participant will be randomly assigned to one of two intervention groups, either the MOBILITY group or the BEDCYC group. Allocation will be concealed within an opaque sealed envelope (Fig. 2). The computer-generated random allocation sequence list will be carried out (JM) using a random-number generator (randomizer.org). Assignments will be enclosed in sequentially numbered, opaque, sealed envelopes and stored at the central study centre. The persons who assess eligibility, obtain informed consent and enrol patients in the trial ([name]) have no knowledge of group assignment. After recruitment, the appropriate numbered, opaque, sealed envelope will be opened and the randomisation information will be given to the patient and therapists (but not to the outcome assessors and not to the statistician performing the analysis).

### Interventions

Patients will be randomly assigned to either the MOBILITY or the BEDCYC (see Fig. 2 and Table 2).

Patients in the MOBILITY group will receive, in addition to standard treatment, 20 min physiotherapy daily. This additional physiotherapy programme includes systematically augmented levels of therapy and mobilisation (Table 3) five times per week, over 2 weeks. The MOBILITY programme contains 10 standardised exercises in hierarchical order (from low grade to higher grade):

**Table 3 Tab3:** Overview of the schedule for increasing the intensity of every therapy session in the MOBILITY group

Session#	Repetitions	Increase^a^	Sets	Rest between sets (s)
1	As many as possible^b^	n.a.	2	120
2	As in previous session + increase	At least by 1	2	120
3	As in previous session + increase	At least by 1	2	120
4	As in previous session + increase	At least by 1	2	120
5	As in previous session + increase	At least by 1	3	90
6	As in previous session + increase	At least by 1	4	90
7	As in previous session + increase	At least by 1	4	90
8	As in previous session + increase	At least by 1	4	60
9	As in previous session + increase	At least by 1	4	60
10	As in previous session + increase	At least by 1	4	45

^a^Therapists chose from our list of 10 standardised exercises the most demanding exercise for every session to adjust for individual differences and physical state on the day of the session

^b^One repetition minimum and a maximum of 10 repetitions even if more repetitions would be possible; if more than 10 repetitions are possible the task (e.g. starting position) itself will be augmented; level 0 means the maximum of repetitions on the first day/first session

Turning from the one side to the other side when lying in the supine position and alternate supine bridging/buttock liftProtracting hands and arms up and down the legs while sittingReach and grasp objects from a table while sittingKnee-bending while standing near the bed with assistanceSit-to-stand exercises as fast as possibleBalance exercises while standing without hand(rail) supportReach and grasp objects from a table while standingStepping while standingWalking on a 10-m indoor floorClimbing stairs

In every therapy session the highest possible of the above-mentioned 10 standardised exercises will be selected. For example, a patient who is able to sit on their own will practice exercise #4, which is bending the knees while standing near the bed with assistance. If the workout of the selected exercise of the MOBILITY programme or the starting position of the exercise is not possible the preceding exercise will be selected by the therapist. For example, a patient who is able to sit on their own but fails to stand up and bend his knees while standing near the bed with assistance, exercise #3 instead of #4 will be selected and trained in therapy.

All 10 exercises will be trained by qualified and instructed therapists and intensity increased progressively according to Table 3. The therapists will document the trained exercises, and total duration and intensity for each single session. The therapy session will be paused/interrupted or terminated if the patient (using continuously monitoring):Has a heart rate below 60 or above 180 beats per min for longer than 3 minHas a persistent SpO_2_ < 88% when lying or sitting for longer than 3 minHas a systolic blood pressure below 100 mmHg or above 180 mmHg for longer than 3 minHas a diastolic blood pressure below 50 mmHg or above 110 mmHg for longer than 3 min

The adherence of the MOBILITY programme will be documented in daily logs and reported.

All single exercises in the MOBILITY programme are well-known and used routinely under different circumstances for the target patients in our department. Our additional MOBILITY programme with systematically augmented levels of mobilisation and therapy is, however, not described in the medical literature yet. For this reason we underwent a pilot training programme testing the feasibility of the MOBILITY programme in our department with all above-mentioned criteria. We found in 10 patients in this pilot training that the MOBILITY programme might be feasible without any adverse event.

### BEDCYC

The BEDCYC group will receive, in addition to standard treatment, 20 min of in-bed cycle ergometer sessions (the same number, frequency and treatment time as the MOBILITY group) [22]. We chose in-bed cycling as comparator to compare two true active and potentially effective interventions. For instance Kho et al. recently described the feasibility and safety of in-bed cycle ergometry as part of routine ICU practice [22]. They described 181 patients on ICU receiving a total of 541 cycling sessions and described a very low (0.2%) event rate and concluded that the use of in-bed cycling as part of routine physical therapy interventions in ICU patients is feasible and appears to be safe [22]. We will use the same in-bed cycle therapy approach as described earlier; however, contrary to the CYCLE pilot protocol of Kho et al. [37] we will use 20-min in-bed cycle ergometer sessions instead of 30-min sessions. BEDCYC will be provided by two experienced therapists who are only providing BEDCYC therapy but not the therapy to the experimental group.

Adherence to the BEDCYC therapy will be documented in daily logs and reported.

To control for cointerventions (standard therapy) during the intervention phase of the study (T0 to T1) therapists will document the total duration and content of both standard and additional therapy. Content will be described for each 5-min block.

### Criteria for discontinuing or modifying allocated intervention in both groups

Therapy sessions will not occur if any of the following conditions are present:Body temperature below 36 °C or above 38.5 °CHeart rate below 40 or above 130 beats per minPersistent SpO_2_ < 90% when lying or sittingMean arterial pressure below 60 mmHg or above 110 mmHgNegative-pressure wound therapyChest drainage systemsCatecholamine medication (vasopressor/inotropes) within the past 2 hActive myocardial ischemia or any unstable arrhythmiaSedation or severe agitation (Richmond Agitation and Sedation Scale score <1 or >2)Uncontrolled painRehabilitation goal has been changed to palliative careRehabilitation team perception that therapy is not appropriate despite absence of the above criteriaRefusal of consent

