### Screening process

We will enter all patients with the diagnosis of a defined CIP and/or CIM into our screening log. Subsequently, the patient will be screened for eligibility with the inclusion and exclusion criteria as outlined in Table 1 and Fig. 2. We will fully inform eligible patients and/or their caregivers about the study, and we will assign an identification number to the patient. Patients and/or their caregivers are then asked to provide informed consent. In the event that a potential participant does not meet the inclusion criteria, we will not retain identifiable information on that patient. We will report all reasons for exclusion in a flow chart. After providing informed consent we will record all medical and neurological information at baseline in a Case Report Form (Table 2).

**Table 1 Tab1:** Inclusion and exclusion criteria of study

Inclusion criteria
1. Patient is in the post-acute phase and chronically critically ill, defined as more than 21 days ICU of treatment including mechanical ventilation, and at least 14 days more in an existing critical situation with the need for ICU treatment [27, 51, 52]
2. Acquired muscle weakness defined as a Medical Research Council (MRC) sum score of <48 points [1]
3. Defined diagnosis of critical illness myopathy (CIM) and/or polyneuropathy (CIP) confirmed by a neurologist according to published diagnostic criteria for CIP/CIM [24]
4. Older than 18 years of age
5. Richmond Agitation Sedation Scale (RASS) score from −1 to 1 [53]
6. Written informed consent of the patient or their legal guardian has been obtained
Exclusion criteria
1. Patients receiving palliative care
2. Comorbidities of the trunk or the lower limbs interfering with upright posture and walking function (e.g. amputation or fracture of lower limb)
3. Other neuromuscular or neurological disease and/or syndromes causing weakness in patients in the ICU (we will exclude patients with diseases and syndromes causing weakness in patients in the ICU [9], due to Guillain-Barré syndrome, myasthenia gravis, porphyria, Eaton-Lambert syndrome, amyotrophic lateral sclerosis, vasculitic neuropathy, cervical myelopathy and botulism)
4. Severe physical comorbidity before becoming critical ill (e.g. frailty due to neurological conditions)

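### The RASS rule for withholding sessions contradicts the RASS inclusion criterion: only a score of 1 satisfies both, and the lower start and in-session limits also fit together poorly

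*Protocol article*

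**What the plan says.** Three places in the protocol article set limits on who may be treated and when.

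- **Table 1, inclusion criterion 5 (Screening process).** Eligible patients have a "Richmond Agitation Sedation Scale (RASS) score from −1 to 1".
- **Criteria for discontinuing or modifying allocated intervention in both groups.** The list opens with "Therapy sessions will not occur if any of the following conditions are present". One entry, labelled as sedation or severe agitation, is a "Richmond Agitation and Sedation Scale score <1 or >2". Other entries bar a session at a heart rate below 40 or above 130 beats per minute, at a mean arterial pressure below 60 or above 110 mmHg, and at a persistent oxygen saturation below 90%.
- **Interventions, MOBILITY text.** A session under way is paused, interrupted or terminated if certain values last longer than 3 minutes. These are a heart rate below 60 or above 180, a systolic pressure below 100 or above 180 mmHg, a "diastolic blood pressure below 50 mmHg or above 110 mmHg for longer than 3 min", or an oxygen saturation below 88%.

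The BEDCYC text states no in-session limits of its own. It refers to a previously described cycling approach and promises the same number, frequency and duration of sessions as MOBILITY.

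**The concern.** A patient can be randomised with a RASS of −1 or 0 and then, on the printed rule, be refused each session for as long as the score stays there. Nothing in the article reconciles the two ranges. The rule applies in both arms, so its direct effect is lost treatment rather than an obvious bias towards one arm.

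That matters because the intention-to-treat analysis is primary and the trial is sized for a 6-point FSS-ICU difference after 2 weeks of treatment. Randomised patients who receive no sessions pull the groups together, and they are the patients most likely to be lost from the per-protocol set. If therapists instead set the printed rule aside because it looks wrong, sessions are given by individual judgement, and adherence cannot be measured against the protocol.

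The secondary issue is narrower. At the lower end, the limits for starting a session are looser than those for continuing a MOBILITY session, so a session can properly start on values that, if unchanged, then interrupt it.

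**Working it through.** The plan reports no figure on this point to reproduce, so the check compares the rules directly.

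**RASS**

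| Score | Eligible (Table 1) | Session allowed (both groups) |
|---|---|---|
| −1 | yes | no (below 1) |
| 0 | yes | no (below 1) |
| 1 | yes | yes |
| 2 | no | yes |

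Eligible scores are {−1, 0, 1}, session-permitted scores are {1, 2}, and the overlap is {1}. At any session, the share of patients withheld who are still within the eligible range is 1 − P(RASS = 1). The article does not give P(RASS = 1). If the three scores were equally common, the share would be 1 − 1/3 = 67%. That is an assumption, and the share could lie anywhere from 0 to 100%.

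**What dilution could do**

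Inputs from the Sample size section: difference 6 points (22 versus 16), SD 10, 45 per arm, two-sample t test, alpha 5% (taken as two-sided). With these inputs power is 80%, as the plan states.

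Assume that a fraction f of patients in each arm receives no sessions at all and contributes no difference between arms. The expected difference is then 6 × (1 − f).

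| f (assumed) | Expected difference | Power, 45 per arm |
|---|---|---|
| 0 | 6 | 80% |
| 1/3 | 4 | about 47% |
| 2/3 | 2 | about 16% |

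The Statistical methods section calls 5 points clinically important. The diluted difference falls below 5 once f exceeds 1 − 5/6, about 17%. These rows show sensitivity only. RASS is judged session by session, so a patient withheld on some days would be partly treated, and the dilution would be smaller.

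**Start limits against in-session limits**

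- *Heart rate, lower end:* a start is allowed from 40 and the in-session floor is 60. Values of 40 to 59 permit a start and meet the MOBILITY stopping rule after 3 minutes if unchanged.
- *Heart rate, upper end:* a start is allowed up to 130 and the in-session ceiling is 180. No value permits a start and also triggers a stop.
- *Blood pressure, lower end:* the start rule uses mean pressure and the in-session rule uses systolic and diastolic pressure. With mean ≈ (systolic + 2 × diastolic)/3, a conventional approximation not given in the article, 95/60 mmHg gives (95 + 120)/3 = 71.7. That is above the start floor of 60, but the systolic value is below 100. The example does not depend on the formula, because mean pressure must lie between 60 and 95. The in-session floor of 100/50 corresponds to (100 + 100)/3 = 66.7, again above the start floor.
- *Oxygen saturation:* a start needs at least 90% and the in-session floor is 88%. There is no conflict. Here the start limit is the stricter one, the reverse of the lower heart-rate and pressure limits.

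**The case against.** **The RASS entry may be a sign slip.** Its label speaks of sedation or severe agitation, and reading every score below 1 as sedation would class two eligible scores as sedated. A dropped minus sign would explain this, and loss in reading the PDF cannot be excluded, although Table 1 kept its minus sign. This is a fair account of how the text may have arisen. It does not remove the need for correction, because the printed threshold decides whether a session takes place.

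**The number affected is unknown.** A reader might infer that most eligible patients are barred, or that most randomised patients would get no study treatment. The article does not support either. Two of three scale values is not a share of patients, no distribution is given, and the rule acts on single sessions. This objection stands in full.

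**The start and in-session rules can both be followed.** They govern different moments, the in-session rule needs more than 3 minutes' persistence, and a pause satisfies it. The team may also withhold a session it judges inappropriate, so no start is compelled. This stands: the lower limits sit awkwardly together, but obeying one does not breach the other. The 10-patient pilot of MOBILITY also found the programme possibly feasible without adverse events, though it is small and says nothing about the RASS rule.

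**The absence of BEDCYC stopping limits is not established.** A reader might infer that low heart rate or pressure would shorten sessions in one arm only, or that safety is undermined. The BEDCYC limits may lie in the cited approach or in the full protocol that the article condenses. Withholding sessions and stricter in-session floors are, if anything, cautious. Daily logs in both arms would also show differences in delivery. Neither an arm imbalance nor a safety failure is shown.

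**Conclusion.** The RASS contradiction holds on the printed text: of three eligible scores, one permits a session and two forbid it, and one non-eligible score is treatable. It rests on reading both thresholds as printed. If a sign was lost, the finding becomes a misprint in an operative rule, which still has to be corrected. Its effect on the trial cannot be sized from the article. The direction is loss of delivered treatment in both arms and dilution of the primary comparison, and the power figures above are conditional on assumed fractions.

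The mismatch at the lower end (heart rate 40 to 59, and low pressures such as 95/60 mmHg) is real but secondary. It calls for clarification and is not a direct contradiction. The scope of the in-session limits for BEDCYC is a question for the sponsor, not an established defect.

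**What to change.** 1. Reconcile the RASS range in Table 1, inclusion criterion 5, with the RASS entry in the section on discontinuing or modifying the intervention, so that every eligible score has an unambiguous session rule.
2. Reconcile the lower heart-rate and blood-pressure limits for starting a session with the in-session limits in the MOBILITY text, or explain why they differ.
3. State whether the in-session limits apply to both groups and, if BEDCYC follows limits set elsewhere, say where.
4. Because recruitment has begun, record which RASS rule therapists have actually applied, and count sessions withheld on RASS grounds by arm from the existing daily logs, as far as those logs give the reason.

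The values are for the clinical leads to decide, and none is proposed here. The cost is a short protocol amendment, an updated therapist checklist and a review of the logs. The design, sample size and analysis do not change.

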### Additional information

The standard care/treatment includes sitting balance exercise, stretching, positioning, sit-to-stand training, transfer training to get out of bed, strengthening exercise (in and outside of bed), stepping and assistive standing exercises as described previously [38]. The standard treatment will be about 45 min daily of individual physical therapy and the duration of therapy will be kept equal in both intervention groups. Total time spent in rehabilitative therapy will be recorded by so-called usual care intervention logs to report the number of physiotherapy and occupational therapy sessions received in the first 2 weeks of the study (as part of the usual care treatment). Information about medication and treatment will be recorded at baseline. Length of stay in ICU and the time spent in post-acute ICU and in rehabilitation will be documented (in days).

As described above, physiotherapists will record in every session the presence of self-reported pain, fatigue, dizziness, number and nature of falls and note other adverse events. The adherence to standard care will be described in daily logs and reported.

### Sample size

Until now, no trials and, therefore, no specific effect size of the selected interventions for this specific population are present in the peer-reviewed literature. Our sample size calculation of 45 patients per study arm is based on a difference of 6 points in the primary endpoint of the FSS-ICU sum score between the parallel groups after 2 weeks of treatment. We assume an alpha level of 5%, a statistical power of 80% (beta = 20%) and a standard deviation (SD) of 10 using a two-sample *t* test for mean differences. Our assumption is based on the theory that the one experimental group achieves a mean of 22 points and the other group achieves a mean of 16 points in the FSS-ICU test assuming a SD of 10 in the FSS-ICU sum score and assuming that the rate of recovery of walking ability will be 0.6 in the one and 0.4 in the other group. We used the SAS (SAS Institute Inc., Cary, NC, USA) power and sample size programme for our sample size calculation. Because we consider a 20% dropout rate, a total of 108 patients (54 per study arm) would be enrolled to ensure 45 subjects in both intervention arms.

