### Statistical methods

We will conduct both intention-to-treat and per-protocol analyses, with the intention-to-treat analysis being always the primary analysis for the primary and secondary outcomes.

Our descriptive statistics will include means and SDs, medians and interquartile ranges for continuous variables, and the number and proportions for categorical variables as appropriate [39].

We will compare the two intervention groups at baseline regarding characteristics and demographics, using two-tailed Student’s *t* tests or Fisher’s exact tests, as appropriate. Variables that differ between the groups at baseline will be considered as possible confounders and adjusted for in subsequent analyses. The global alpha level will be set at 0.05 for all comparisons. To avoid multiplicity we will use a Tukey-Kramer alpha adjustment for multiple comparisons of the same outcome. Skewed data will be analysed with nonparametric test alternatives (e.g. we will use the Mann-Whitney *U* test instead of Student’s *t* tests if data are skewed).

For the primary endpoint, the FSS-ICU, we will test the hypothesis that the sum score after 2 weeks of intervention and at follow-up will be statistically different between groups. We will consider a minimum difference of 5 points of the FSS-ICU sum score (range 0–35 points) between groups as being clinically important.

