### Ethics and dissemination

The FITonICU study will be conducted in accordance with the Helsinki Declaration. The study is noninvasive, imposes no additional risk on patients, seems to have enough power to detect meaningful determinants and our protocol has been approved by the medical ethical committees (ethical vote ‘Landesärztekammer Sachsen’ Germany; EK-BR-104/15-1). Furthermore, written informed consent is obtained from all participants or, if necessary, from a legal guardian ([name]). We registered our study on 6 April 2016 before enrolling the first patient in the trial at the German Clinical Trials Register (www.germanctr.de/) with the identifier DRKS00010269.

We plan to disseminate the results of this study to the scientific, medical and general public by publication in national and international peer-reviewed journals, as well as by presentations at conferences and meetings with clinicians working with patients with ICUAW.

Authorship will follow the recommendations of the International Committee of Journal Editors for authorship. No professional writers will be employed.

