### Limitations

One could argue that the lack of a true control group, e.g. of standard or no additional physiotherapy, might be a weakness of our trial protocol. We have, however, designed this study to compare two potentially capable and reasonable active physical rehabilitation interventions for patients on ICU. The feasibility and safety of BEDCYC was established in previous studies [37] and is a promising physical rehabilitation intervention for patients on ICU. The efficacy and effectiveness relative to standard treatment alone for BEDCYC will be investigated in other RCTs [37, 50]. The MOBILITY intervention is not yet described in the literature, but MOBILITY was tested over several months at our department and seems a feasible physical rehabilitation intervention for patients on ICU. We decided not to introduce a ‘classical’ control group in our study, because there is no such classical control treatment in the ICU, but there is a need for effective therapy to be conducted to explore the role of physical rehabilitation interventions for people with CIP and CIM.

The second limitation is that this trial is planned to be carried out as a single-centre study and can, therefore, only be seen as a first or pilot study. This pilot trial is, however, adequately powered and funded. Further RCTs should, however, try to recruit further centres and hospitals to increase the clinical knowledge about physical rehabilitation interventions for people with ICUAW.

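### The sample size gives 80% power for FSS-ICU only; at the protocol's own 0.6 versus 0.4 rates, the unqualified claim of adequate power does not hold for the other primary endpoint, walking ability

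*Protocol article*

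**What the plan says.** The Abstract and the Outcome measures section make walking ability and FSS-ICU both primary efficacy endpoints, with no order between them.

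According to the Sample size section, the figure of 45 per arm "is based on a difference of 6 points in the primary endpoint of the FSS-ICU sum score between the parallel groups". The other inputs are listed there too: "We assume an alpha level of 5%, a statistical power of 80% (beta = 20%) and a standard deviation (SD) of 10". The method named is a t test comparing two means. A further sentence gives the assumed FSS-ICU means (22 and 16) and, in the same breath, the walking assumption: "assuming that the rate of recovery of walking ability will be 0.6 in the one and 0.4 in the other group". The section gives no time point for these rates, and no test, event count or power for walking.

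The Statistical methods section analyses walking as time from T0 to FAC 3, by Kaplan-Meier, log-rank and Cox, with censoring at discharge, treatment refusal or death. Intention-to-treat is the primary analysis.

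The Limitations section states: "This pilot trial is, however, adequately powered and funded". It does not say for which endpoint.

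**The concern.** The walking rates stand among the sample-size assumptions but play no part in producing 45. A reader who sees both primary endpoints in that paragraph, followed by a general statement of adequate power, will take the sample size as covering both.

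What is at stake is how a non-significant walking result will be read. The trial compares two active interventions, so a null finding from a trial described as adequately powered invites the conclusion that they are equivalent for walking. If power at the planned effect is well below 80%, that result would be inconclusive.

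**Working it through.** **Inputs from the protocol.** Sample size: alpha 5%, power 80%, SD 10, difference 6, walking rates 0.6 and 0.4, 45 evaluable and 54 enrolled per arm. Study design: 1:1 allocation. Statistical methods: log-rank test for walking. Sidedness is not stated for the sample size; two-tailed testing is named only for the baseline comparisons ("using two-tailed Student’s" tests). Two-sided is used here because 45 reproduces only that way: a one-sided test would need 35 per arm.

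**Step 1: the stated figure (FSS-ICU).**
- Normal approximation: n = 2 × (1.960 + 0.842)² × (10/6)² = 43.6, so 44 per arm.
- Noncentral t: 44.6, so 45 per arm, with 80.4% power at 45.

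The stated 45 is right for FSS-ICU.

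**Step 2: walking as a comparison of proportions.** The mean rate is 0.5.
- Power = Φ{[0.2√n − 1.960√(2 × 0.5 × 0.5)] / √(0.6 × 0.4 + 0.4 × 0.6)}.
- n = 45: (1.342 − 1.386)/0.693 = −0.064, power 47% (46% by exact enumeration of the chi-square test).
- n = 54: (1.470 − 1.386)/0.693 = 0.121, power 55%.
- For 80%: n = (1.386 + 0.842 × 0.693)²/0.2² = 96.9, so 97 per arm.

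**Step 3: walking by the planned log-rank test.** Take 0.6 and 0.4 as the proportions walking at the end of observation.
- Under proportional hazards, HR = ln(1 − 0.6)/ln(1 − 0.4) = 0.916/0.511 = 1.79, with ln HR = 0.584.
- Expected events at 45 per arm: 27 + 18 = 45.
- Schoenfeld power = Φ(√events × 0.584/2 − 1.960).
- 45 events: √45 × 0.292 = 1.960, power 50% (simulation of 20,000 trials: 49.9%).
- 54 events (all 54 per arm kept): 2.147 − 1.960 = 0.187, power 57%.
- Events for 80%: 4 × (1.960 + 0.842)²/0.584² ≈ 92.

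**Step 4: the range if the rates apply at 2 weeks.** Suppose events continue at the same hazards beyond that point. At k times the follow-up, expected events are n × [(1 − 0.4^k) + (1 − 0.6^k)].

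| Follow-up | Per arm | Expected events | Log-rank power (Schoenfeld) | Simulated |
|---|---|---|---|---|
| 2× | 45 | 45 × (0.84 + 0.64) = 67 | 67% | 66% |
| 4× | 45 | 45 × (0.974 + 0.870) = 83 | 76% | 75% |
| 2× | 54, no loss | 80 | 74% | 74% |
| 4× | 54, no loss | 100 | 83% | 83% |

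Reaching 92 events means that 92/108 = 85% of all randomised patients are observed to regain walking.

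**The case against.** The strongest defence is that nothing in the calculation is wrong. The Sample size section ties 45 per arm and the 80% to the FSS-ICU t test. A reader might infer that the protocol claims 80% power for walking and has miscalculated it, but it makes no such statement. This part of the defence stands. The defect is the general adequacy claim, together with a second primary endpoint that the calculation does not cover.

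Second, the low figure depends on reading 0.6 and 0.4 as final proportions. FAC is also recorded daily and at follow-up visits, and a time-to-event analysis gains power as events accrue. This too stands, so saying flatly that the planned walking effect would be missed about half the time goes beyond the document. It does not rescue 80% at 45 per arm: 76% is reached only at four times the follow-up.

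Third, a reader might infer that 80% is unattainable because 92 events exceed the 90 evaluable patients. That is not supported. All 108 randomised patients enter the intention-to-treat log-rank test and contribute until censored, so 92 events are possible. They are unlikely, given censoring at discharge, refusal or death and the protocol's own 20% dropout allowance.

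Fourth, the Limitations section also describes the trial as a first or pilot study, which tempers the claim somewhat but leaves the adequacy sentence unqualified. The remark under Ethics and dissemination that the study "seems to have enough power to detect meaningful determinants" concerns determinants and is hedged, so it is not evidence of a power claim for the walking comparison.

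**Conclusion.** The point holds as a statement that is wrong as written, not as an arithmetic error. At 45 per arm the trial has 80.4% power for FSS-ICU. For walking, at the protocol's own rates and two-sided 5%, power is about 47% (proportions) or 50% (log-rank) if the rates are final proportions, and 55–57% if nobody is lost. If they are 2-week rates with continuing events and proportional hazards, log-rank power at 45 per arm is about 67–76%. Only the combination of no loss and prolonged accrual, with about 92 or more walking events, reaches 80%.

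These figures assume a two-sided test and, for the log-rank test, proportional hazards. The time point of the rates is the main unknown, and the protocol must supply it. How far censoring limits event accrual cannot be determined from the document.

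**What to change.** 1. In Sample size, state that 45 per arm gives 80% power for FSS-ICU only.
2. Give the time point to which 0.6 and 0.4 refer, and the resulting log-rank power for walking with its assumed number of events: about 50% if they are final proportions at 45 per arm.
3. In Limitations, restrict the adequacy statement to FSS-ICU.
4. State that a non-significant walking result will be reported as inconclusive, with the hazard ratio and its confidence interval.

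These are changes of wording and need no extra patients. The price is that the stated power for walking becomes less favourable.

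Making walking a key secondary endpoint tested after FSS-ICU would match the calculation actually done, but it is optional. In a registered trial that is already recruiting, it is a substantive design change, and the correction does not depend on it.
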